#### Dissemination

The results of the study will be published in a peer-reviewed medical journal without using the services of a professional writer. Once agreed by the Steering Committee, the source data will be made available to share through national or international anonymized datasets.

## Discussion

The preservation of fertility and the integrity of the reproductive organs is increasingly of concern to women with adenomyosis. Due to the disadvantage of medical treatments, adenomyomectomy was now increasingly applied. Remission from dysmenorrhea or dyspareunia after complete excision of the lesion has been reported as 50–94.7% and improvement in menorrhagia as 25–80% [18]. Nevertheless, a symptomatic or local recurrence of the condition may occur. About 2.8–13.95% of patients relapsed at the end of first year in this study; 14.28–49% of patients had recurrence of disease in the following 24 months [18]. Therefore, the long-term management after surgery is the main issue to be addressed.

Recently, AI Jama retrospectively analyzed 18 patients who underwent adenomyomectomy and treatment with GnRHa for 24 weeks, 15 of whom had systematic improvement after 1 year of follow up [16]. Liu carried out a non-controlled descriptive study of 186 women with pathologically proven adenomyoma, who underwent ultramini-laparoscopic adenomyomectomy and a 6-month course of goserelin acetate treatment. The rate of systematic recurrence was 9% after 3 years of follow up [19]. Wang et al. identified a significant decline in the relapse rate in the surgical-medical treatment group at the end of 2-year follow up in a prospective, non-randomized study [7]. However, our retrospective analysis showed no difference between the control and intervention group at the end of the first or second year. It is noteworthy that there was a significant difference between the control and the GnRH agonist group in symptomatic relapse or relapse as identified on imaging studies at the end of the 36-months follow up. In other words, postoperative treatment might be applied to reduce the long-term recurrence rate. Whether or not we should use the postoperative method to prevent relapse in patients with adenomyosis is still unknown.

This is the first multicenter, prospective, randomized controlled trial, comparing the efficacy of GnRH agonist in reducing recurrence in patients with focal adenomyosis who have undergone adenomyomectomy. We cannot blind the trial participants and care providers to treatment allocation due to the drug-induced amenorrhea and/or series of side effects after GnRHa therapy, which will help patients and doctors identify the treatment. The lack of blinding might cause substantial bias, especially in the subjective judgment of patients, such pain scoring for the primary outcome. To solve this problem, we set up two types of pain scoring system to reduce the chance of subjective error judgment among patients. In addition, recurrence of dysmenorrhea is defined according to the patient’s pain score and the need for changes in treatment, which can better evaluate progress after conservative treatment. We plan to enroll 308 participants from 10 teaching hospitals in China. The enrollment began in March 2018. At the time of manuscript preparation, more than 90 subjects have been enrolled. The result of this large multicenter randomized trial will provide level-I evidence for the strategy of long-term management of focal adenomyosis after conservative surgery.

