### Screening and enrollment

Previous medical history and current medication status are reviewed in the standardized case report forms. A physical examination and imaging such as two/three-dimensional color doppler ultrasonography (2D/3D-CDUS) or magnetic resonance imaging (MRI) are performed. Laboratory measurements include measurement of serum follicle-stimulating hormone (FSH), estradiol (E2), anti-Muellerian hormone (AMH), cancer antigen 125 (CA125), and safety assays including routine analysis of blood, urine, liver function, renal function, hepatitis virus, HIV, syphilis, and coagulation; electrocardiogram (ECG) and radiography are performed in the local departments at the study sites. Either laparoscopy or transabdominal surgery is performed to completely remove all clinically recognizable lesions in patients who are suspected to have focal adenomyosis.

Written informed consent will be obtained from the patients after surgery. Quality of life, degree of pain, and menstrual volume will be recorded using the Short Form (36) Health Survey (SF-36), Female Sexual Function Index (FSFI), pictorial blood loss assessment chart (PBAC) score, visual analogue scale (VAS) and numeric rating scale (NRS) after confirming by histologic assessment. A schedule of enrollment, interventions, and assessment is provided Table 1.

**Table 1 Tab1:** Schedule of screening, enrollment and assessment

Evaluation	Screening	Enrollment	Time of follow up after surgery (month)						
			3	6	12	18	24	30	36
Written consent		√							
Inclusion/exclusion criteria		√							
Medical history	√								
Physical exam	√								
Safety test (preoperative examination)	√								
2D/3D-CDUS/MRI	√		√	√	√	√	√	√	√
FSH, E_2_, AMH, CA125	√		√	√	√	√	√	√	√
Side effects			√	√	√	√	√	√	√
VAS and NRS		√	√	√	√	√	√	√	√
SF-36 and FSFI		√	√	√	√	√	√	√	√
PBAC score		√	√	√	√	√	√	√	√

*2D/3D-CDUS/MRI* two/three-dimensional color doppler ultrasonography/magnetic resonance imaging, *FSH* follicle stimulating hormone, *E*_*2*_ estradiol, *AMH* anti-Muellerian hormone, *CA125* cancer antigen 125, *VAS* visual analogue scale, *NRS* numeric rating scale, *SF-36* Short Form-36 Health Survey, *FSFI* Female Sexual Function index, *PBAC* pictorial blood loss assessment chart

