### Randomization

Eligible participants are assigned by simple randomization in a 1:1 ratio to one of two groups. The sequence of randomization has been set up by biostatisticians in the data coordination center using Microsoft Excel and the “RAND ()” function. The original sequence is safely kept by the staff in the data coordination center, and it has been put into the online central randomization system by these staff members, who are not involved in enrolling subjects. The sequence is not accessible to any investigators or study coordinators. If a subject fulfills the enrollment criteria, the authorized study coordinator will obtain the assignment for her. After randomization, both subjects and investigators are informed about the assignments.

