### Outcome and outcome assessments

The primary outcome is relapse, which is defined as recurrence of dysmenorrhea or pelvic pain, or menorrhagia, or local recurrence compared to the first follow up after surgery as confirmed by 2D/3D-CDUS/MRI. Relapse as identified by 2D/3D-CDUS or MRI constitutes an increase > 1 cm in the maximal diameter of the suspected recrudescent focus during the follow-up period. The VRS and NRS are also applied for evaluation of dysmenorrhea or pelvic pain and the recurrence is defined as any increase in the scores and by participants asking for other medical treatments for relief of symptoms at the same time during follow up. The PBAC score is used to predict coagulation disorders in women with menorrhagia and recurrence is defined as a score > 100. The proportion of participants with recurrence at 3, 6, 9,12, 18, 24, 30, and 36 months will be recorded.

The secondary outcomes include quality of life, clinically confirmed pregnancy, ovarian reserve, and adverse events (AE). Quality of life is assessed by the SF-36 and FSFI, as measures of health status and sexual functioning in women. Ovarian reserve is evaluated by measuring FSH, E_2_, and AMH; the first two are measured before surgery and during the follow-up period at the beginning of the menstrual cycle unless the participant is currently receiving treatment with triptorelin acetate. AMH can be measured at any time before and after surgery at the time of follow up. Differences in scores for eight dimensions (physical functioning, role-physical, bodily pain, general health, vitality, social functioning, role emotional and mental health) of the SF-36 and for the FSFI, and the mean values of FSH, E_2_, and AMH for will be recorded for assessment of quality of life and ovarian reserve participants in each group of participants at 3, 6, 9,12, 18, 24, 30, and 36 months. The participant’s intention to become pregnant, the pregnancy rate, and outcome are recorded in a standard case report form, including details of abortion, premature delivery, and full-term delivery, to evaluate differences in pregnancy outcomes in each treatment arm at 36 months.

The follow-up procedure is acquired from the outpatient department records. Follow-up visits occur at 3, 6, 12, 18, 24, 30, and 36 months after conservative surgery.

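### Neither stated safeguard removes reporting bias from the pain component, and the either/or composite carries that bias into the primary result

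*Protocol article*

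**What the plan says.** Under Outcome and outcome assessments: "The primary outcome is relapse, which is defined as recurrence of dysmenorrhea or pelvic pain, or menorrhagia, or local recurrence", so any one component makes a woman a primary event. The components are:

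- **Pain:** "recurrence is defined as any increase in the scores and by participants asking for other medical treatments for relief of symptoms at the same time". No minimum rise is set.
- **Menorrhagia:** a PBAC score above 100.
- **Imaging:** "an increase > 1 cm in the maximal diameter of the suspected recrudescent focus during the follow-up period".

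Under Randomization: "After randomization, both subjects and investigators are informed about the assignments". The Data analysis plan blinds the data analysts. The article mentions no other masking.

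The Discussion names the risk itself: "The lack of blinding might cause substantial bias, especially in the subjective judgment of patients, such pain scoring for the primary outcome". It then gives two answers. The first is "To solve this problem, we set up two types of pain scoring system to reduce the chance of subjective error judgment among patients". The second is that recurrence of dysmenorrhea depends on the need to change treatment as well as on the score.

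Table 1 schedules imaging and both pain scales at every follow-up visit from month 3 to month 36.

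**The concern.** An open-label design is not the error here. The article explains why it cannot blind women or care providers, and it discloses the consequence. The error is the claim that the consequence has been dealt with.

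A second self-rating by the same person reduces random error. It leaves untouched any shift that comes from knowing the allocation, because that shift enters both ratings. The treatment limb is no more independent: the operative rule counts the woman's own request, and she and her clinician both know whether she had surgery only.

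If women in one arm report pain or ask for treatment more readily because of what they know, the composite differs between arms without any drug effect. A larger sample does not help, since it only makes a biased difference more likely to reach significance. A positive result could then be read as efficacy, on the strength of a safeguard that cannot work.

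**Working it through.** **Inputs from the protocol article.** 139 per group, two-sided alpha 0.05 (Sample size calculation); Pearson chi-square on the 3-year recurrence rate (Data analysis plan).

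**The plan's own figure.** For 49% v 28.1% at 85% power, the usual two-proportion formula gives 96 per group (106 with continuity correction), not 139. At 139 the power is about 95%. That discrepancy is a separate matter. Here 139 is taken as the planned number analysed.

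**Assumptions (no figure in the documents).** No true effect; a common relapse rate of 30%, 35% or 40%; extra reported relapse in group A of 5 or 10 percentage points on the composite.

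**Step 1: does a second scale remove a shift?** Assume two scales with SD 1, correlation 0.8 and a common reporting shift of 0.5 SD.

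- Mean of the two scales: the shift stays at 0.50. The SD falls only to √((1 + 0.8)/2) = 0.95.
- One scale above a 1 SD cut-off: the shift raises the share from 15.9% to 30.9%.
- Both scales above that cut-off: from 9.8% to 21.8%.

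Requiring both scales lowers the event rate, but the shift still about doubles it.

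**Step 2: effect on the primary test.** With p̄ = (pA + pB)/2, SE0 = √(2p̄(1 − p̄)/n) and SE1 = √((pA(1 − pA) + pB(1 − pB))/n), the rejection probability is about 1 − Φ((1.96·SE0 − d)/SE1), where d = pA − pB; the opposite tail is negligible when d is 10 points.

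Example, 40% v 30%: SE0 = √(2 × 0.35 × 0.65/139) = 0.0572; SE1 = √((0.24 + 0.21)/139) = 0.0569; (1.96 × 0.0572 − 0.10)/0.0569 = 0.213; rejection ≈ 0.416. Summing exact binomial probabilities over the chi-square rejection region gives 0.421.

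| Common true rate | No bias | +5 points in group A | +10 points in group A |
|---|---|---|---|
| 30% | 0.050 | 0.144 | 0.421 |
| 35% | 0.051 | 0.142 | 0.399 |
| 40% | 0.050 | 0.130 | 0.379 |

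**Step 3: dilution through the composite.** If a share q relapses on objective components in both arms, independently of pain, the composite rate is 1 − (1 − q)(1 − pain rate). With an assumed q = 20% and reported pain relapse of 30% v 20%, this is 1 − 0.8 × 0.7 = 44% v 1 − 0.8 × 0.8 = 36%. Ten points on pain become eight on the composite, and rejection is about 27%. The composite dilutes the bias but does not remove it.

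**Step 4: direction.** Six courses at 4-week intervals put the last injection 5 × 4 = 20 weeks after the first, so the month-3 visit falls within group B's treatment. The outcome definition refers to the first follow-up after surgery, but its grammar leaves open whether that reference applies to pain or only to local recurrence. If it applies to pain, a drug-suppressed reference score makes a later rise more likely in group B, which acts against triptorelin.

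**The case against.** The strongest defence is that the article is candid about the risk, offers a two-part answer, and includes an imaging component with a fixed threshold. It is also a condensed account of a fuller protocol. The candour deserves credit, and the treatment limb is a genuine second hurdle: a score rise alone is not an event. But that hurdle is also set by an unblinded woman's decision, so the claim to have solved the problem still fails.

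Some stronger readings are tempting but not supported:

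- **That the scans are read unmasked.** The article says investigators know the allocation. It says nothing about the sonographer or MRI reader, and the full protocol may. The correct statement is that reader masking is not stated.
- **That the pain rule is met by almost any stable woman.** Over several visits most would exceed their reference once by chance, but the rule needs the rise and the request at the same time. At a single visit, with assumed noise SD of 0.5 to 1.5 points on a 0–10 scale, simulation gives about 24–41% for one scale. The score limb therefore excludes most stable women at any one visit.
- **That the bias must favour triptorelin.** Over-reporting after surgery alone would do so; a suppressed month-3 reference would do the reverse.
- **That the pain scale is unidentified.** The outcome section says VRS where Table 1 says VAS, but the Abstract spells VRS out as visual analogue scale. This is a labelling slip for editorial correction.

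**Conclusion.** The concern holds. The article identifies a real threat to its primary outcome and claims to solve it with measures that all come from the same unblinded woman. With no true effect, an assumed 5-point reporting difference on the composite raises the false-positive rate at 139 per group from 5% to 13–14%, and a 10-point difference to 38–42%, for true rates of 30–40%. If the 10 points arise in the pain component alone, with 20% objective relapse in both arms, the figure is about 27%.

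These bias sizes are assumptions, and nothing in the documents says how large the bias will be. They show how sensitive the test is and do not predict the result. They also take the bias to raise reporting in group A, while the net direction is uncertain.

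**What to change.** 1. State that the readers who already perform the scheduled scans are not told the allocation and record focus diameter before any clinical discussion, with the same modality for each woman where possible. If the full protocol already provides for this, say so.
2. Prespecify imaging-confirmed relapse, with the existing 1 cm criterion, as a key secondary endpoint. Report each component of the composite by arm. State that a positive composite driven only by patient-reported components will be interpreted as open to reporting bias.
3. Replace the sentence claiming a solution with a statement that two scales reduce random error only and that reporting bias remains. Correct VRS to VAS.

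**Cost.** A site instruction and some wording, with no extra visits or scans. Imaging-only relapse has fewer events and so less power. Masking may be imperfect at months 3 and 6, where the Interventions section uses ultrasound to help monitor adherence, so that use should be kept apart from the diameter reading.

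**Not proposed.** A rule accepting the composite only if imaging points the same way gives limited protection: with 10 points of bias and an assumed 20% imaging relapse in both arms, false positives fall only from 38–42% to 27–32%. A minimum score rise addresses noise rather than expectation, and would change the primary endpoint after more than 90 women were enrolled.

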### Data analysis

#### Sample size calculation

Sample size was determined based on data from a prospective study demonstrating a relapse rate of about 49% in the group that received surgery alone and 28.1% in the group that received surgery and GnRH agonist treatment [7]. A two-tailed test with alpha set at 0.05 and 85% power is used to detect a minimum clinically meaningful difference between control and intervention groups. The minimal sample size is calculated as 139 participants in each group. In consideration of a dropout rate of 10%, we will recruit 308 participants in total.

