**Fig. 1 Fig1:**
[figure not shown]
Flowchart of this study

Intention to treat, which is based on the initial treatment intent, will be used as a foundation in our analysis. Participants who begin the allocated treatment are part of the trial, whether they finish it or not. The characteristics at baseline will be compared between the control and intervention groups. Continuous data will be summarized by the mean and standard deviation and the Wilcoxon rank sum test will be used to identify differences in baseline characteristic between the two groups. Categorical data will be described by number and percentage, using the Pearson chi-square test to compare data from the two groups.

The primary outcome measure is the difference in the recurrence rate between group A and group B after 3 years of follow up, which will be analyzed by the Pearson chi-square test. For efficacy parameters, such as the score for pelvic pain and dysmenorrhea, menstrual blood loss, and the size of the uterus and the lesion, will be analyzed using generalized estimating equations (GEE) or mixed effects model repeated measures (MMRM) to account for correlation among these observations at different follow-up points.

The variables from secondary outcomes, including scores on the SF-36 and the FSFI, the pregnancy rate, and pregnancy outcomes, are calculated during 36 months of follow up using GEE or MMRM analysis to compare groups A and B to identify differences between groups at different time points. The number of participants with adverse events (AE) or serious adverse events (SAE) will be calculated in each arm and taken into final statistical testing.

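### Two pain scales completed by the same unblinded woman do not remove the open-label bias that the article admits in the primary outcome

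*Protocol article*

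**What the plan says.** All places are in the protocol article.

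- *Randomization*: once allocated, "both subjects and investigators are informed about the assignments".
- *Discussion*: "The lack of blinding might cause substantial bias, especially in the subjective judgment of patients", with pain scoring for the primary outcome given as the example. The remedy follows at once: "To solve this problem, we set up two types of pain scoring system to reduce the chance of subjective error judgment among patients". A second safeguard is added: recurrent dysmenorrhea depends on the pain score together with a need to change treatment.
- *Outcome and outcome assessments*: relapse is an either/or composite of pain, menorrhagia or local recurrence. The pain limb needs any rise in the scores plus a request by the participant for other treatment. The menorrhagia limb is a PBAC score above 100. The imaging limb is growth of more than 1 cm in the largest diameter of the suspected focus.
- *Data analysis plan*: "The primary outcome measure is the difference in the recurrence rate between group A and group B after 3 years of follow up", tested by Pearson chi-square. Pain scores, menstrual blood loss, and uterine and lesion size are also compared over time by GEE or MMRM. Blinding is stated for data analysts.

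**The concern.** The article names a systematic error, and the remedy it offers acts on random error. If knowing the allocation changes how a woman rates her pain, it changes both of her ratings. If it changes how readily she asks for further treatment, the second safeguard shifts as well. The threshold on the score is any increase, so the request does much of the work in deciding whether a pain event is counted.

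The requirement for confirmation by ultrasound or MRI reads most naturally as belonging to local recurrence only. Pain without imaging change can therefore make a primary event. The trial asks whether the drug lowers disease recurrence, and the *Discussion* promises the highest grade of evidence on that question. A difference that arises in reporting would enter the primary test as recurrence, and a reader of the article would believe this had been dealt with.

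**Working it through.** **1. Inputs from the article (*Sample size calculation*).** "A two-tailed test with alpha set at 0.05 and 85% power is used to detect a minimum clinically meaningful difference"; "relapse rate of about 49% in the group that received surgery alone and 28.1% in the group that received surgery and GnRH agonist treatment"; "The minimal sample size is calculated as 139 participants in each group". With 10% dropout allowed for, the planned total is 308.

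**2. The plan's own figure.** With pooled variance, p̄ = (0.49 + 0.281)/2 = 0.3855 and

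n = [1.960·√(2·0.3855·0.6145) + 1.036·√(0.49·0.51 + 0.281·0.719)]² / 0.209² = 95.8, so 96 per group (106 with continuity correction).

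The stated 139 is not reproduced at 85% power; 139 per group gives about 95%. That is a separate matter. I use 139 per group below because it is the evaluable number the article plans for. Dropout: 278/0.9 = 309, against 308 stated.

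**3. What a second scale does.** Let each score carry the same reporting shift δ and unit variance, with correlation ρ between the scales.

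- Bias of the mean of two scores: (δ + δ)/2 = δ, a reduction of 0%.
- Variance of the mean: (1 + ρ)/2. With ρ = 0.8 (assumed) this is 0.90, a reduction of 10%.

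A simulation of 400,000 draws with ρ = 0.9, a shared shift of 0.3 SD and an illustrative cut-off of 0.8 SD (all assumed) gives this false gap between arms:

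| Rule | No shift | With shift | False gap |
|---|---|---|---|
| One scale | 21.2% | 30.9% | 9.7 points |
| Either scale | 26.4% | 37.2% | 10.8 points |
| Both scales | 16.0% | 24.5% | 8.5 points |

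No way of combining the two scales brings the gap near zero.

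**4. Effect on the primary test.** Assume true relapse of 40% in both arms, 139 per group, and extra reported relapse in one arm only. For a 10-point gap, p̄ = 0.45, the null SE is √(2·0.45·0.55/139) = 0.0597, and the SE under the shifted rates is √((0.50·0.50 + 0.40·0.60)/139) = 0.0594. Then

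Φ[(0.10 − 1.96·0.0597)/0.0594] = Φ(−0.286) = 0.388.

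Exact enumeration of the two-sided 0.05 Pearson test gives:

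| Reporting gap (assumed) | Significant results, base 40% | Base 28.1% |
|---|---|---|
| 0 points | 5.0% | 5.0% |
| 5 points | 13.0% | 14.8% |
| 10 points | 37.9% | 42.7% |
| 15 points | 70.2% | 75.1% |

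**5. The same through the composite.** Assume objective relapse of 20% in both arms, and pain-only relapse among the remaining women of 20% against 10%. Reported relapse is 0.20 + 0.80·0.20 = 36% against 0.20 + 0.80·0.10 = 28%. The exact test rejects in 29.8% of trials.

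**6. Scale.** If 68 of 139 relapse in group A, significance needs 51 or fewer in group B: 17/139 = 12.2 points, against a planned effect of 49 − 28.1 = 20.9 points.

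**7. Direction.** *Outcome and outcome assessments* refers to the first follow-up after surgery as the reference. This certainly applies to local recurrence and possibly to symptoms. By Table 1 that visit is month 3, when group B is expected to be part-way through its six four-weekly injections. A low pain score there would make any later increase more common in group B, against the drug.

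**The case against.** The strongest reply has four parts.

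- **It is wording in a Discussion.** The article admits the bias openly, and the sentence itself aims only to lower the chance of error. It also names the treatment-request safeguard. This stands in part: the admission is candid, and the request does narrow the pain limb. But the article presents the problem as solved, and neither safeguard is independent of knowing the arm.
- **Component tables belong in the SAP.** An absent table alone would be no finding. The finding is a stated remedy that cannot do what is claimed for it; the supportive analysis is the repair.
- **The domains are already analysed separately.** A reader might infer that the composite is all the plan looks at. That is not so: the GEE or MMRM analyses of pain, blood loss and lesion size would partly show where a difference lies. None of them, however, compares the imaging relapse event between arms, and a repeated mean of lesion size is not that event.
- **The magnitudes are invented.** The base rate and gaps are assumptions, and any open-label trial with a patient-reported endpoint would give such a table. This stands. The figures show what is possible, not what is likely.

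Three further readings are tempting and not supported. No section says who completes the PBAC, so it cannot be called a self-report. Imaging is not a neutral arbiter, because investigators know the arm and the article mentions blinding for data analysts only. Nor would it help to claim reduced recurrence only when the imaging difference points the same way. In the 10-point scenario with equal imaging relapse of 10–20% in both arms (assumed), 61–71% of the false-positive composites favouring the drug would still pass such a rule.

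**Conclusion.** The point holds in this form. The stated safeguard does not address the bias the article admits, because two self-reports by one unblinded woman share any shift due to allocation, and her request for treatment is made with the same knowledge. Since pain alone can be a primary event, differential reporting can move the primary chi-square. For gaps of 5, 10 or 15 points on equal true relapse of 40% with 139 per group, the chance of a significant result is 13%, 38% or 70% instead of 5%.

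These figures rest on an assumed base rate and an assumed gap. The article gives no size for the reporting effect and no relapse rate for imaging alone. A reader might infer that the trial is likely to yield a false positive in favour of the drug; the article does not support that, and the month-3 reference could push the bias the other way and hide a real effect. It should be corrected before results are known, but it does not invalidate the primary analysis.

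**What to change.** 1. In the *Discussion*, withdraw the statement that two pain scales solve the problem. Say instead that they reduce random error, and that bias from open treatment remains in the pain limb.
2. In the *Data analysis plan*, pre-specify one supportive analysis: the difference between arms in relapse by the imaging limb alone (growth above 1 cm) over 36 months, with a 95% CI, shown beside the composite and each symptom limb. Table 1 already schedules imaging at every follow-up visit.
3. State how it will be read: if the composite difference comes mainly from the symptom limbs, the conclusion will describe it as relapse including patient-reported symptoms under open-label treatment. Attach no rule that the imaging difference must agree in direction.
4. State that the imaging limb depends least on self-report but is not free of bias, since the article mentions blinding for data analysts only.

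The cost is one extra table and a few sentences. The imaging limb has fewer events, so its interval will be wide: with 139 per group and imaging relapse of 10% or 20% in both arms (assumed), the half-width is 1.96·√(2·0.10·0.90/139) = 7.1 points or 1.96·√(2·0.20·0.80/139) = 9.4 points. It is therefore supportive and not a second hurdle. The primary test, alpha and sample size stay as they are.
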